### Participants

#### Recruitment of ICUs

The participating ICUs belong to the French Society of Critical Care (SRLF) or the French Society of Anesthesiology (SFAR). The selection criteria were:Adult, medical, surgical or medical-surgical ICU patientsAgreement of the whole team to write in the diariesSupervision of the study by physicians or nursesAgreement with the randomized design in the ICUs which previously used diaries

The participating ICUs are displayed in Additional file 2.

#### Recruitment of patients

Inclusion criteria are as follows:Age 18 years or olderMechanical ventilation for more than 48 h and initiated within the first 48 h after ICU admissionPatient having a family member speaking and understanding French, and with the ability to visit them during the ICU staySubject consenting to participate in the study, or obtention of family consent in case of patient incompetency

Non-inclusion criteria are as follows:Patient without family availablePatient or family not speaking or understanding FrenchCurrent or previously neurologic conditions that would preclude questionnaire completion such as pre-existing psychotic or dementia-type illness, hospitalization after a cardiac arrest, acute neurologic diseases (meningitis, ischemic or hemorragic stroke), or cerebral trauma patientsPatient status considered by the investigator to be inevitably leading to death or to withdrawal of life support within 48 hPatient already included in a study with interview follow-upPatient deprived of libertyDeaf and mute patients

### Intervention

The intervention is the elaboration of an ICU diary by caregivers and families. All the diaries for every center are built on the same way by the main investigator and given to the different centers before the beginning of the study. The first page is standardized and includes an explanation of the purpose of the diary; then the diary includes a picture of a typical patient’s room with an explanation of the different devices possibly used during the stay, pictures of the unit, and a list of the main responsible persons of the unit. The diary is maintained by the family and by the ICU staff. The only instruction given to the families and staff members about diary entries is to refrain from writing about confidential matters that could not be shared among the patient, all relatives, and the staff. Staff members are free to express compassion and their hope, or absence thereof, that the patient would recover. Relatives can speak freely with the patients without guidance from the ICU staff. The first entry is written immediately after randomization by the ICU physician and includes a summary of the reason for admission, the name of the ICU and of the hospital, and a summary of the events of the first 48 h. Then, each day, a brief entry is mandatory during the whole ICU stay. This entry can be done by an ICU staff member whatever their category. Relatives are not encouraged to take photos of the patient during the whole stay without the patient’s permission. No patient’s photos taken during the ICU stay are allowed in the ICU diary, only pictures taken prior to the ICU stay (which were taken with the patient’s authorization). For patients in the intervention arm, they received the ICU diary at the conclusion of their ICU stay when they are discharged to wards. If the patient dies, the diary is given to the family if they are present in the unit or sent by mail with an identical letter for all ICUs. A guide for the elaboration of the ICU diary was given to each center containing: rules for writing in the diary, indications for opening and maintaining the diary, for writing that the patient status does not fit well when the clinical patient status impaired, and for relinquishing the diary at ICU discharge. Examples of verbatim narratives of different categories of healthcare workers (ICU physician, resident, nurse, nursing assistant, physiotherapist) are included in the guide. World Health Organization Trial registration Data Set is provided in Additional file 3.

### Training

A training on the study will be performed for each center by the main investigator at the study initiation visit. A meeting is planned, enabling the supervisors of the study to discuss the training with the ICU staff. The study will be presented and the guide of how to fill in the diaries will be discussed. Examples of verbatim narratives will be provided. A free discussion will be organized to address all potential difficulties for the ICU staff. The phone numbers of the main investigator ([name]) and of the two clinical researchers will be provided to each center for managing issues during the inclusion period. During the study period, the local co-investigator in each center is responsible for the supervision and promotion of the study, and supports the ICU staff for all potential difficulties for writing in the diaries.

### Arms

#### Intervention arm

An ICU diary is opened by the ICU staff for the patient and their relatives at 48 h after ICU admission. It will be given to the patient at ICU discharge or to his family in case of death.

#### Control arm

No diary is commenced during the ICU stay.

### Randomization

The 1:1 randomization is stratified by center and balanced with permutation blocks. Randomization is performed via a secure and dedicated website managed by the ICUREsearch company. Family members or patients are randomized at 48 h after ICU admission if they fulfill all inclusion and non-inclusion criteria.

### Data collection

#### ICU characteristics

The following ICU characteristics are recorded: hospital (university, community or private hospital), ICU (medical, surgical or medical-surgical), number of beds, structure of the unit (number of senior physicians and resident, nurse-to-patient ratio, nursing assistant-to-patient ratio).

#### Patient characteristics

The following patient characteristics are recorded: demographics (sex, age); health status before ICU admission (Knaus [47] and McCabe [48] classification), health status at ICU admission using the Simplified Acute Physiology Score [49], type of admission (medical, scheduled surgical, or emergency surgical); use and duration in days of mechanical ventilation, of non-invasive ventilation, sedation duration, iatrogenic events, length of ICU stay. The date and limitation of treatments are also collected.

#### Family characteristics

The following family characteristics are recorded: age, gender, relationship with the patient, educational level, professional status.

### Sample size justification

Post-traumatic stress-related syndrome was reported in 15% [35], 20.7% [50], 51% [19], and 64% [22] of patients and in 29.8% [50], 42% [51], 49% [52], and 67% [22] of family members of ICU patients. We hypothesized that patient PTSD rate will be 40% in the control group and 26% in the intervention group. To detect such a difference between the two groups with a type 1 error of 0.05 and a power of 80%, it is necessary to interview 352 patients (176 in each group) at 3 months. At 3 months, considering a mortality rate of 40% and a cumulative rate of 50% of re-hospitalization or impossibility of interviewing the patient (refusal, sequelae or impossibility to join them), we will include 700 patients and their family member in the 35 centers. In each center, 20 patients will be included (10 in the intervention arm, i.e., with an ICU diary, and 10 in the control arm).

### Statistical analysis

#### Outcome analysis

The analysis will be done according to the intention-to-treat principle. In each randomization group, we will report summary statistics according to the data (median and interquartile range, percentage with a 95% confidence interval).

The quantitative data will describe the patient’s characteristics and the results of the psychological impact using the IES-R and HADS scales in the two arms. The impact of ICU diaries on PTSD will be assessed using a Mantel-Haenszel chi-square test.

A Kruskal-Wallis test will be used to compare quantitative secondary endpoint.

In case of disequilibrium of patient characteristics between groups, further multivariate analyses will be computed.

To explain the effect of patient state of health, family characteristics and patient PTSD on both anxiety and depression, an exploration of direct and indirect effect of each variable on secondary outcomes will be performed using mediation analysis based on a structural equation model [53]. This approach consists of distinguishing measured variables which are indicators of unmeasured (latent) variables and exogenous variables which are exposure factors. Two steps will be performed: (1) an explanatory analysis to identify the latent variables and their measures and (2) the confirmatory analysis to assess direct or indirect relations between each latent variable. This second step is based on a conceptual model which clearly explains the relations between latent variables and their measures and defines the pathway between latent variables (Fig. 2). Because PTSD, anxiety, and depression will all be measured by a score, this approach will be more relevant to consider the different explicative factors. PTSD will be introduced as a latent variable to explain anxiety and depression [54, 55]. Finally, the center effect could be considered by introducing a hierarchical level in the mediation analysis. This point will be explored during the exploratory analysis.

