**Methods:**

A prospective, multicenter, randomized, assessor-blind comparative study of the effect of an ICU diary on patients and families. We will compare two groups: one group with an ICU diary written by staff and family and given to the patient at ICU discharge or to the family in case of death, and a control group without any ICU diary. Each of the 35 participating centers will include 20 patients having at least one family member who will likely visit the patient during their ICU stay. Patients must be ventilated within 48 h after ICU admission and not have any previous chronic neurologic or acute condition responsible for cognitive impairments that would hamper their participation in a phone interview. Three months after ICU discharge or death of the patient, a psychologist will contact the patient and family by phone. Post-traumatic stress syndrome will be evaluated using the Impact of Events Scale-Revised questionnaire, anxiety and depression symptoms using the Hospital Anxiety and Depression Scale questionnaire, both in patients and families, and memory recollection using the ICU Memory Tool Questionnaire in patients. The content of a randomized sample of diaries of each center will be analyzed using a grid. An interview of the patients in the intervention arm will be conducted 6 months after ICU discharge to analyze in depth how they use the diary.

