The secondary objectives are to evaluate:The PTSD in families 3 months after ICU discharge, using the IES-R scale [42]. The criteria of measurement will be the score of PTSD as having a low or high IES-R score, using 22 as the cutoff, as previously used in ICU studies [43]Anxiety and depression symptoms in patients 3 months after ICU dischargeAnxiety and depression symptoms families 3 months after ICU discharge. Symptoms of anxiety and depression are assessed using the validated French version of the self-administered Hospital Anxiety and Depression Scale (HADS), which has seven items on anxiety and seven on depression [44]. The sum for each domain ranges from 0 to 21. A score at 7 or below is considered normal. The cutoff score of 8 for each of the two subscales defines severe symptoms of anxiety or depression [45]The recollection of memories of the ICU stay by the patient 3 months after ICU discharge, as measured by the ICU Memory Tool Questionnaire [46]. The ICU Memory Tool Questionnaire consists of items exploring recollections of the patient before and during their ICU stay. It also includes two questions to assess if PTSD symptoms are present. As no French version exists, the ICU memory tool questionnaire was translated and back-translated into French by bilingual researchers, namely a French native who speaks English and an English native who speaks FrenchDiary content analysisThe content of a random sample of the study diaries will be analyzed with a grid (Table 1) that has already been published [22]. This grid was built with a panel comprising 11 members (three ICU physicians including two from other units, one ICU nurse, two psychologists, two hospital visiting volunteers, one person from the general population with a history of admission to another ICU, one former patient of our ICU, and his wife) using a Delphi technique. Six categories were defined and will serve for the analysis of the content of the diaries. We will report quantitatively the categories and themes which are represented most often in the diaries and will give verbatim examples for each of them.

**Table 1 Tab1:** Grid of analysis of the content of the intensive care unit (ICU) diary

Category 1: Defining places, spaces, and people	
Theme 1	Narrative about the ICU and its location in the hospital and city
Theme 2	Narrative about the identity and job responsibilities of each ICU staff member
Theme 3	Narrative about the characteristics of the room

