**Fig. 2 Fig2:**
[figure not shown]
Example of a path diagram

All the analyses will be stratified by center. Data will be analyzed with the software SAS 9.4 (SAS Institute Inc., Cary, NC, USA). The results will be reported using the Consolidated Standards of Reporting Trials (CONSORT) criteria.

Figure 2 reports an example of a path diagram. Five latent variables are considered: (1) patient status of health, measured by ICU admission variables; this is supposed to impact the PTSD, but also anxiety and depression; (2) the ICU diary is considered here as a latent variable which can impact PTSD, anxiety and depression; (3) PTSD can have a direct effect on anxiety and depression; (4) anxiety, and (5) depression are the outcome and are considered inter-dependent. The model allows assessing direct effect between latent variables but also indirect effect, such as the effect of the ICU diary on anxiety which is mediated by PTSD.

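### The Kruskal-Wallis test named for quantitative secondary endpoints has no centre term, against the plan's own rule that every analysis is stratified by centre; the cost is modest conservatism and some lost power.

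*Protocol article*

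**What the plan says.** All references are to the protocol article.

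- **Randomization:** "The 1:1 randomization is stratified by center and balanced with permutation blocks".
- **Statistical analysis, Outcome analysis:** for the binary PTSD outcome, "The impact of ICU diaries on PTSD will be assessed using a Mantel-Haenszel chi-square test". For the other scores, "A Kruskal-Wallis test will be used to compare quantitative secondary endpoint".
- **Statistical analysis, text below the Fig. 2 caption:** "All the analyses will be stratified by center".
- **Outcome analysis, on the structural equation model:** "Finally, the center effect could be considered by introducing a hierarchical level in the mediation analysis". Apart from the general rule, this is the only mention of centre in the analysis section, and it is optional.
- **Abstract and Sample size justification:** there are two arms and 35 centres, and "In each center, 20 patients will be included (10 in the intervention arm, i.e., with an ICU diary, and 10 in the control arm").

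**The concern.** Kruskal-Wallis ranks all patients together. With two groups it is the unstratified Wilcoxon rank-sum test, and its standard form has no stratum argument. The Mantel-Haenszel test chosen for PTSD is different, because it can carry centre as its stratum. The rule on stratification therefore fits the primary test but not the test named for quantitative secondary endpoints.

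Stratified randomisation balances the arms within centres, so differences between centres largely cancel from the arm comparison. A test that ignores centre still counts those differences as noise. It then overstates the variance of the comparison, gives p-values that are somewhat too large, and forgoes precision that the design has already provided. At stake is the sensitivity of comparisons such as the anxiety and depression scores, not the validity of a positive finding.

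**Working it through.** **1. The plan's own figure.** The choice of test rests on no stated figure, but the sample size sets the scale. With 40% vs 26%, two-sided 0.05 and 80% power, the mean proportion is 0.33 and

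n per arm = [1.96·√(2·0.33·0.67) + 0.8416·√(0.40·0.60 + 0.26·0.74)]² / 0.14² = (1.303 + 0.553)² / 0.0196 ≈ 176.

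That gives 352 in total, as the protocol states. I therefore take about 350 interviewed (700 × 0.5, or 10 per centre). As a low case I take 700 × 0.6 × 0.5 = 210, which applies both of the protocol's loss rates.

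**2. Assumptions that are not in the document.** Scores are normal, the shift is 0.3 of the total SD, and the centre ICC runs from 0 to 0.30.

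**3. Size of the unstratified test, by formula.** The test behaves as if the variance of the arm difference were proportional to 1. If each centre contributes equal numbers per arm, the true value is 1 − ICC. If a share p of the randomised patients is interviewed at random, some imbalance returns and the true value is 1 − p·ICC. The type I error is about 2·[1 − Φ(1.96/√(true value))]. At ICC 0.20:

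- Equal numbers per centre: 1.96/√0.80 = 2.19, giving 0.028.
- Half interviewed at random: 1.96/√0.90 = 2.07, giving 0.039.

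**4. Simulation with exactly 5 per arm in each of 35 centres.** The comparator is a plain centre-stratified rank test (van Elteren).

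| ICC | KW type I error | KW power | Stratified rank power |
|---|---|---|---|
| 0 | 0.051 | 0.78 | 0.74 |
| 0.05 | 0.045 | 0.79 | 0.75 |
| 0.10 | 0.042 | 0.79 | 0.78 |
| 0.20 | 0.029 | 0.80 | 0.82 |
| 0.30 | 0.021 | 0.82 | 0.87 |

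The stratified test kept a type I error of 0.046 to 0.050 throughout.

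**5. Simulation with random attrition.** Here 10:10 are randomised per centre and each patient is interviewed with probability p. The comparator is a linear model with arm and a random centre intercept (20,000 null runs and 10,000 alternative runs per cell).

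| p | ICC | KW type I error | KW power | Model type I error | Model power |
|---|---|---|---|---|---|
| 0.5 | 0 | 0.054 | 79% | 0.055 | 81% |
| 0.5 | 0.10 | 0.045 | 79% | 0.052 | 83% |
| 0.5 | 0.20 | 0.039 | 79% | 0.051 | 86% |
| 0.3 | 0 | 0.050 | 56% | 0.052 | 59% |
| 0.3 | 0.10 | 0.045 | 56% | 0.049 | 61% |
| 0.3 | 0.20 | 0.042 | 56% | 0.052 | 65% |

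**6. Reading the results.** Because the shift is fixed in total SDs, Kruskal-Wallis power stays level while the adjusted analysis gains. The loss is relative to what the design could deliver. The model's lead of about 2 points at ICC 0 owes nothing to centre; it reflects the normal scores assumed. Of the 7-point gap at p = 0.5 and ICC 0.20, roughly 7 − 2 = 5 points are due to centre.

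**7. The alternative of rank tests within centre.** An aligned-rank test (scores centred within centre, then ranked) reached about 84% at p = 0.5 and ICC 0.20. At p = 0.3 and ICC 0 it lost power against Kruskal-Wallis, at 51% vs 56%.

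**The case against.** The strongest reply is that the stratification sentence governs every test named above it. The Mantel-Haenszel sentence does not name its stratum either. Read in the same way, the Kruskal-Wallis comparison would be run as its stratified relative, the Cochran-Mantel-Haenszel row-mean-score test on ranks, and the exact variant could be left to the analysis plan. That reading is possible. But the text is not silent here: it names a test whose standard form breaks the rule. The candidates that would satisfy the rule (van Elteren, aligned ranks, a model with centre) can also give different p-values. The most literal candidate, the plain stratified rank test, has lower power than Kruskal-Wallis at low ICC (step 4), so the choice matters.

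A second reply is that the power loss depends on an ICC that nobody has stated. This stands. With small centre effects there is little to regain, and some stratified tests would do worse.

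A reader might infer more than the document supports:

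- **That secondary results would be falsely positive.** The reverse holds, since the error is at or below the nominal level apart from simulation noise.
- **That the primary result is affected.** The Mantel-Haenszel test can take centre as its stratum.
- **That the HADS cut-off of 8 contradicts a quantitative test.** Aims gives both a 0 to 21 score and a cut-off, and the Kruskal-Wallis sentence is limited to quantitative endpoints. Both can be reported, and the label given to scores of 8 or more changes no result.
- **That the absence of an effect size from Kruskal-Wallis is an error.** A test is not an estimator, and summaries by arm are planned.

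**Conclusion.** The inconsistency is real: the named test omits the factor that the randomisation uses and that the plan says every analysis will use. It is a modest point about secondary endpoints.

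At an assumed ICC of 0.20 and about 350 interviewed, Kruskal-Wallis has a type I error of 0.029 (equal numbers per arm in every centre) to 0.039 (random attrition). Under random attrition its power is about 79%, against about 86% for a centre-adjusted model. At an ICC near 0 the difference is negligible once the advantage from normal scores is set aside. These sizes rest on an assumed ICC, an assumed shift of 0.3 SD, normal scores and attrition unrelated to outcome. HADS subscales are bounded, so the model's lead over a rank test may be smaller in practice. The contradiction in the text depends on none of these assumptions.

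**What to change.** Replace the Kruskal-Wallis sentence with a centre-adjusted comparison of each quantitative secondary score. The preferred form is a linear model with arm and a (random) centre term, reporting the between-arm difference with its 95% CI. If a rank analysis is wanted, name one centre-stratified rank test as a sensitivity analysis. State its downside: with few interviewed patients per centre and small centre effects, stratified or aligned-rank tests can lose a few points of power.

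The cost is one or two sentences in the analysis plan, settled before the data are examined. The model runs in the SAS 9.4 already specified. Sample size, data collection and the primary analysis do not change.

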**Fig. 2 Fig2:**
[figure not shown]
Example of a path diagram

All the analyses will be stratified by center. Data will be analyzed with the software SAS 9.4 (SAS Institute Inc., Cary, NC, USA). The results will be reported using the Consolidated Standards of Reporting Trials (CONSORT) criteria.

Figure 2 reports an example of a path diagram. Five latent variables are considered: (1) patient status of health, measured by ICU admission variables; this is supposed to impact the PTSD, but also anxiety and depression; (2) the ICU diary is considered here as a latent variable which can impact PTSD, anxiety and depression; (3) PTSD can have a direct effect on anxiety and depression; (4) anxiety, and (5) depression are the outcome and are considered inter-dependent. The model allows assessing direct effect between latent variables but also indirect effect, such as the effect of the ICU diary on anxiety which is mediated by PTSD.

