## Abstract

**Background:**

Post-intensive care syndrome includes the multiple consequences of an intensive care unit (ICU) stay for patients and families. It has become a new challenge for intensivists. Prevention programs have been disappointing, except for ICU diaries, which report the patient’s story in the ICU. However, the effectiveness of ICU diaries for patients and families is still controversial, as the interpretation of the results of previous studies was open to criticism hampering an expanded use of the diary. The primary objective of the study is to evaluate the post-traumatic stress syndrome in patients. The secondary objectives are to evaluate the post-traumatic stress syndrome in families, anxiety and depression symptoms in patients and families, and the recollected memories of patients. Endpoints will be evaluated 3 months after ICU discharge or death.

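### The exploratory mediation model calls the randomised diary latent, and its PTSD-mediated effect on anxiety rests on two assumptions that one 3-month contact cannot test

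*Protocol article*

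**What the plan says.** Under Outcome analysis, the protocol article plans an exploratory mediation analysis of secondary outcomes with a structural equation model. It describes the approach as "distinguishing measured variables which are indicators of unmeasured (latent) variables and exogenous variables which are exposure factors". So latent means unmeasured, and exposures are exogenous. It adds that "PTSD will be introduced as a latent variable to explain anxiety and depression". There are two steps: the first is "an explanatory analysis to identify the latent variables and their measures", and the second, labelled confirmatory, assesses the relations between the latent variables.

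The text with Fig. 2, offered as an example diagram, lists five latent variables and says that "the ICU diary is considered here as a latent variable which can impact PTSD, anxiety and depression". It names as one quantity of interest an "indirect effect, such as the effect of the ICU diary on anxiety which is mediated by PTSD".

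Two other places matter. Under Randomization: "The 1:1 randomization is stratified by center and balanced with permutation blocks". In the Abstract: "Endpoints will be evaluated 3 months after ICU discharge or death". The Aims section places patient IES-R and patient HADS at that single 3-month time point, and the Abstract describes a psychologist's phone contact for them. The only later contact, at 6 months, is a qualitative interview in the diary arm.

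**The concern.** There are two separate problems.

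**The label.** Allocation is known without error. A variable that is known for everyone is not latent in the article's own sense. The Fig. 2 text gives patient health status its measures (admission variables) but gives the diary none.

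**The mediated effect.** The mediator and the outcome are scored at the same contact, so nothing in the design shows that PTSD symptoms come before anxiety. Randomising the diary protects the arm effect on each score. It does not protect the path from PTSD to anxiety, because PTSD itself is not randomised. A shared distress factor, or anxiety feeding PTSD symptoms, would produce the same data.

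At stake is what the trial may say about mechanism. The model as described can return a diary effect on anxiety that runs through PTSD when no such effect exists.

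**Working it through.** **1. The plan's own figure.** The mediation analysis has none. The only related figure is 352 interviewed patients (176 per arm) for 40% against 26%. Two-sided 0.05, 80% power, pooled variance, no continuity correction:

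n per arm = [1.960·√(2·0.33·0.67) + 0.842·√(0.40·0.60 + 0.26·0.74)]² / 0.14² ≈ 176.

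It reproduces and does not bear on this point.

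**2. The label.** Set side by side, Outcome analysis reserves latent for unmeasured variables with measured indicators and treats exposures as exogenous. Randomization makes the diary a known 1:1 assignment. The Fig. 2 text lists it as latent. What follows depends on how it would be fitted:

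- Arm as sole indicator, loading fixed at 1 and error at 0: the latent variable equals the arm. Harmless but redundant.
- Arm as sole indicator, error left free: one known quantity (the variance of arm) against at least two unknowns (latent variance and error variance), so 1 − 2 = −1 degrees of freedom. The arm indicator alone does not identify that part of the model.
- Other indicators chosen after randomisation, such as diary use or content: the path is no longer the randomised contrast.

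**3. Direction.** Reduce the model to arm, PTSD and anxiety:

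- Planned: PTSD = a·arm + e₁; anxiety = c′·arm + b·PTSD + e₂; indirect effect = a·b; total = c′ + a·b.
- Reversed: anxiety first, then PTSD on arm and anxiety.

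Each has three paths and two residual variances and reproduces the same covariances, so fit cannot separate them. A simulation with n = 400,000 and illustrative standardised coefficients (assumptions, not from the article) gave:

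| Truth | True indirect effect via PTSD | Planned model: indirect | Planned model: direct | Total arm effect on anxiety: true / estimated |
|---|---|---|---|---|
| A. PTSD drives anxiety, no confounding | −0.18 | −0.180 | 0.000 | −0.18 / −0.180 |
| B. Anxiety drives PTSD | 0 | −0.110 | −0.192 | −0.30 / −0.302 |
| C. Common cause, residual correlation 0.3 to 0.8, no diary effect on anxiety | 0 | −0.091 to −0.237 | +0.087 to +0.239 | 0 / −0.004 to +0.002 |
| D. Common cause, residual correlation 0.3 to 0.7, diary effect −0.3 on both scores | 0 | −0.088 to −0.211 | −0.208 to −0.089 | −0.30 / −0.297 to −0.301 |

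The log-likelihoods of the planned and reversed models agreed in every case (difference 0.000).

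Case B by hand: a = 0.6 × (−0.3) = −0.18. Within arm, the covariance of the scores is 0.6 and the variance of PTSD is 0.36 + 0.64 = 1, so b = 0.6 and a·b = −0.108.

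**4. Size under one common factor.** Let the diary shift a distress factor F by δ. Let each score equal √ρ·F plus independent error, with within-arm variance 1. Then:

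- a = δ√ρ and total c = δ√ρ;
- within-arm covariance of the two scores = ρ, so b = ρ;
- a·b / c = ρ.

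The share credited to PTSD is the within-arm correlation, whatever δ is. A simulation of 352 patients (2,000 runs, δ = −0.39) gave 0.505, 0.602, 0.704 and 0.801 for ρ = 0.5, 0.6, 0.7 and 0.8.

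**The case against.** The strongest reply is that this is an exploration of secondary outcomes, illustrated by an example diagram. It is not a claim that PTSD mediates anything. The article says that such a model allows an indirect effect to be assessed. It cites sources for placing PTSD upstream (not available here), bases the second step on a conceptual model, includes health status at admission, treats anxiety and depression as inter-dependent and contemplates a centre level. All of this stands, and it rules out several stronger readings:

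- *The protocol asserts mediation.* It does not; it plans to estimate it.
- *The indirect effect cannot be identified at all.* Too absolute. Case A recovers it exactly when the direction and the absence of confounding hold.
- *A latent diary throws away the randomisation.* Only if indicators other than the arm are used, or if arm is treated as error-prone. The text does not say that, and Fig. 2 is not visible.
- *Half or more of any mediated effect will be spurious.* The 50% to 80% restates an assumed correlation in a simplified model without health status, depression or centre. It is not a forecast for this trial.
- *Fit and p-values will be optimistic because constructs are found and confirmed in the same patients.* The article describes no separate sample. But the conceptual model and the named scores fix much of the measurement part, and further detail may sit in the analysis plan.

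The reply does not remove the core. Calling the analysis exploratory does not make the direction testable. Adjusting for admission status handles only the confounding that it measures. The second step is still labelled confirmatory.

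**Conclusion.** The point holds in a limited form. The latent label contradicts the article's own definitions and should be corrected. The diary effect on anxiety through PTSD is estimable only under two assumptions, that PTSD drives anxiety and that nothing confounds the pair, and scores from one contact can test neither. Under a single common distress factor, the share wrongly credited to PTSD equals the within-arm correlation: 50% to 80% at assumed values of 0.5 to 0.8. Under a reversed direction, the illustrative model reported −0.11 where the truth was 0.

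The total arm effect on anxiety was recovered in every scenario. The primary Mantel-Haenszel test and the direct arm comparisons are untouched. The matter is of modest weight: it limits what the trial may conclude about mechanism, not whether the diary works.

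**What to change.** - Enter randomised arm as an observed binary exogenous variable and correct the Fig. 2 text to say so.
- Report the total arm effect on IES-R, HADS anxiety and HADS depression as the randomised result.
- State the direction and no-confounding assumptions, and show the reversed-direction model, or a sensitivity analysis for mediator–outcome confounding, beside the planned one.
- Report the PTSD-to-anxiety and PTSD-to-depression paths as associations under those assumptions.
- Do not present the second step as confirmatory evidence of mediation.

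No new data are needed. The cost is some extra analysis and wording, and a more modest statement about mediation.
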